### Safety assessments

Emergency telephone contact with the investigators will be available for any questions or problems related to the treatment. On day 5 of the treatment, the participant will receive a call, text, or email from one of the investigators to determine and record compliance, side effects, BV symptoms, and satisfaction with treatment. The study pharmacist will be informed by the recruiting clinician of the participant’s full name, date of birth, and personal health number, and the study number assigned, so that the study pharmacist can enter the medication name into the British Columbia PharmaNet Database (the provincial pharmacy database). This safety measure ensures that subsequent treating physicians throughout the province will have access to details of the treatment received, in case of a safety concern and a need to unblind the participant’s medication should the participant present with an emergency. Non-emergency access to the provincial pharmacy database is not allowed, to protect the participant’s identification of the blinded treatment.

If at any time the participant reports intolerable side effects (vaginal discomfort, intolerable vaginal discharge, urticaria, or secondary yeast infection) during treatment, or exacerbation of symptoms at any point, she may voluntarily discontinue the treatment and leave the study without prejudice, and her doctor or another physician may provide treatment as per usual standard of care.

As neither metronidazole nor H_3_BO_3_ treatments provided to patients are in amounts considered toxic when taken intravaginally or if accidentally ingested, should there be any occurrence of serious adverse effects (neurological, cardiac, respiratory, gastrointestinal, or anaphylactic reactions) during any of the treatments, the study will be put on hold until an investigation can be held. In the case of serious adverse effects found to be caused by the treatment, the study will be stopped, and the study unblinded and decoded by the study pharmacist. The investigators, participants, and clinicians involved in the study would be informed for the reason for stopping the study.

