### Outcomes and assessment

On days 17–19 and days 40–42, if the vaginal swab is positive for BV found by both meeting three of four Amsel criteria and having a Nugent score ≥7 and the participant is symptomatic for BV, the physician will prescribes a standard medication of his choice. This is considered a treatment failure addressing our primary and secondary outcomes: effectiveness at 7 days and 30 days after treatment end.

If the participant discontinued the treatment during the 10 days because of side effects or complained of intolerable side effects (major adverse effects) from the treatment, this is considered a treatment failure referring to our secondary outcome: safety.

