### Statistical considerations

The primary outcome measure is a non-inferiority per-protocol comparison of effectiveness of H_3_BO_3_ with metronidazole at day 17, as measured by Nugent score, in 16–50-year-olds with a *z*-based confidence interval for the difference of two proportions. This was chosen as the primary outcome measure because the immediate effect of H_3_BO_3_ after a 10-day treatment compared with metronidazole was our most important question about BV treatment. A change from a baseline Nugent score ≥7 to a Nugent score <7 is considered a cure of BV. Treatment failure will be reported as a positive Nugent score ≥7 at day 17.

Secondary outcome measures include a non-inferiority intention-to-treat comparison of effectiveness of H_3_BO_3_ with metronidazole at day 17, as measured by Nugent score in 16–50-year-olds, with a *z*-based confidence interval for the difference of two proportions. We will use this comparison to confirm the robustness of our per-protocol comparison but the per-protocol analysis will be the primary determinant of the non-inferiority test. In addition, we will conduct a non-inferiority comparison of effectiveness of H_3_BO_3_ and metronidazole at day 40, as measured by Nugent score in 16–50-year-olds analyzed on both per-protocol and intention-to treat principles, with a *z*-based confidence interval for the difference of two proportions, and safety consideration including intolerable adverse effects requiring patient discontinuation of the 10-day treatment. To control for multiple testing, we will use a Bonferroni-type correction. To account for both intention-to-treat and per-protocol analyses, and two timepoint analyses, the threshold for statistical significance will be set at 0.01 (approximately 0.05 divided by 4).

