The following are tertiary outcome measures and no formal sample size calculations were made. Minor adverse effects (side effects not causing the patient to discontinue treatment) will be reported and compared between the treatment arms but will not be considered as treatment failure. We will examine the adolescent population, the 16–19 year old subgroup, for non-inferiority for effectiveness of H_3_BO_3_, as compared with metronidazole, at the end of the study. Finally, we will test for superiority of the effectiveness and safety of H_3_BO_3_ compared with placebo in both the 16–50-year-olds and in the 16–19 year old subgroup. In addition, our study is the first to be able to examine 16–19-year-olds for the effectiveness and safety of metronidazole compared with placebo.

95 % confidence intervals will be established. Missing data (participants who fail to complete follow-up for any reason) are accounted for by an anticipated 25 % lost-to-follow-up rate. Data will be blindly collected by the outcome assessors from the participating clinics and entered into an electronic database. The study pharmacist will provide the randomization code for the data to a third-party statistician and the data will be analyzed. Self-reported participant satisfaction criteria included at the end of the daily treatment diary will use a five-point rating scale to record: effectiveness in curing BV symptoms, side effects, ease of use, likelihood they would use it again for BV treatment, likelihood they would recommend it to someone else for BV treatment.

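### The per-protocol analysis settles non-inferiority and intention-to-treat cannot overturn it; if clearly more women leave on boric acid, the claim can stand although the all-randomised difference is beyond the margin

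*Protocol article*

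**What the plan says.** All references are to Methods/Design in the protocol article.

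- **Decision rule (Statistical considerations).** "The primary outcome measure is a non-inferiority per-protocol comparison of effectiveness of H_3_BO_3_ with metronidazole at day 17". Its weight is then spelled out: "the per-protocol analysis will be the primary determinant of the non-inferiority test". The intention-to-treat comparison at day 17 is secondary and has a supporting role: "We will use this comparison to confirm the robustness of our per-protocol comparison". Nothing says what follows if the two disagree.
- **Leaving (Safety assessments).** A woman with intolerable side effects, or with worsening symptoms, is told that "she may voluntarily discontinue the treatment and leave the study without prejudice", and may then receive usual care.
- **How stopping is counted (Outcomes and assessment).** Of stopping during the 10 days because of side effects, the article says "this is considered a treatment failure referring to our secondary outcome: safety".
- **Efficacy failure (Statistical considerations).** "Treatment failure will be reported as a positive Nugent score ≥7 at day 17". This needs a day-17 swab.
- **Missing follow-up (Statistical considerations).** "Missing data (participants who fail to complete follow-up for any reason) are accounted for by an anticipated 25 % lost-to-follow-up rate". This is an allowance in the sample size, not a rule for counting these women.
- **Alpha (Statistical considerations).** "To account for both intention-to-treat and per-protocol analyses, and two timepoint analyses, the threshold for statistical significance will be set at 0.01", described as roughly 0.05 divided by 4.

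**The concern.** A woman who leaves because the treatment is intolerable or the infection gets worse is a poor result for that treatment. Under the article's definitions she supplies no day-17 Nugent score, her stopping for side effects is assigned to the safety outcome, and she probably drops out of the set that decides the trial. The deciding comparison is then between women who tolerated and completed treatment. If leaving differs by arm, that comparison no longer rests on randomised groups, and the analysis that would show the problem has no stated power to block the claim.

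The alpha arrangement does not fit this hierarchy. Dividing alpha between two analysis sets protects against either one winning alone. If per-protocol decides, intention-to-treat needs no share; if both must succeed, neither needs one. The plan pays for two sets without giving intention-to-treat a say in the conclusion.

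**Working it through.** **1. The plan's own figure.** Inputs from Study design: margin 10 points, one-sided 95% interval, 80% power, true advantage 8 points. Metronidazole cure is taken as 75%, the middle of the stated 70–80%, so boric acid is 83%.

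n = (z₀.₉₅ + z₀.₈₀)² × [p_M(1−p_M) + p_B(1−p_B)] / (p_B − p_M + 0.10)²

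= (1.645 + 0.842)² × (0.1875 + 0.1411) / 0.18² = 62.7, so 63 per group. The stated 63 is reproduced.

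**2. Excess leaving needed to reach the margin.** Let d_B and d_M be the proportions leaving, and count leavers as not cured. The all-randomised difference is p_B(1−d_B) − p_M(1−d_M).

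- Completers equal at 75%: d_B − d_M = 0.10/0.75 = 13.3 points.
- Completers 83% v 75%, d_M = 10%: 0.83(1−d_B) = 0.675 − 0.10 = 0.575, so d_B = 30.7%, an excess of 20.7 points. Over metronidazole cure of 70–80% and d_M of 5–25%, the excess is about 18 to 23 points.

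**3. A case beyond the margin.** 80 per arm; completers 75% in both arms; leaving 20% (boric acid) v 5%. The leaving rates are assumptions.

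- True all-randomised cure: 0.75 × 0.80 = 60% v 0.75 × 0.95 = 71.25%; difference −11.25 points.
- Per-protocol, 64 v 76 women: SE = √(0.1875/64 + 0.1875/76) = 0.0735. The chance that the lower limit exceeds −10 points is about Φ(0.10/0.0735 − 1.645) = Φ(−0.28) = 39% at one-sided 0.05, and Φ(1.36 − 2.326) = 17% at 0.01. Simulation with random numbers of leavers (400,000 runs) gives 39 to 40% and 18%.
- All randomised: SE = √(0.60×0.40/80 + 0.7125×0.2875/80) = 0.0746. The chance is Φ(−0.0125/0.0746 − 1.645) = Φ(−1.81) = 3.5% at 0.05. In simulation, requiring both sets gives about 4% at 0.05 and 0.7% at 0.01.

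**4. The planned 8-point advantage in completers.** With 83% v 75% and leaving 31% v 10%, the true all-randomised difference is 0.83×0.69 − 0.75×0.90 = −10.2 points. Per-protocol declares non-inferiority in 80% of trials at 0.05 (58% at 0.01); requiring both gives about 5% (1%).

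A single data set shows the same. Boric acid: 26 of 80 leave, 45/54 completers cured. Metronidazole: 8 of 80 leave, 54/72 cured. Per-protocol difference +8.3 points, lower limit −3.5 at 0.05 and −8.4 at 0.01: non-inferior at either level. All randomised: 45/80 − 54/80 = −11.25 points.

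**5. Equal leaving.** With 83% v 75% and 25% leaving in each arm, the all-randomised difference is 0.75 × 8 = +6 points. The harm does not arise.

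**6. Power cost, using one intention-to-treat definition.** Completers 83% v 75%, 80 per arm. In each arm 20% are lost at random and left out of intention-to-treat, a simple stand-in for imputation. Of the remaining women, 5% leave for treatment-related reasons and count as not cured.

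| One-sided alpha | Per-protocol alone | Both required |
|---|---|---|
| 0.05 | 79% | 72% |
| 0.025 | 69% | 60% |
| 0.01 | 56% | 46% |

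If instead all of a 25% loss per arm counted as failure, joint power would be 61% at 0.05 and 48% at 0.025.

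**The case against.** Per-protocol analysis is a customary part of a non-inferiority assessment, and it was declared primary in advance. Intention-to-treat at day 17 is also prespecified, and discontinuation for intolerance is a secondary outcome, so a discordant result would be visible to readers. That is fair, and naming per-protocol as primary is not an internal contradiction. What stands is that the rule for the claim itself does not depend on the second analysis.

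Some stronger readings are tempting and are not supported:

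- **That boric acid is less well tolerated, so the trial will produce a false claim.** The documents give a single 25% dropout rate, not split by arm or reason, and nothing on comparative tolerability. At 15% v 5% leaving with 83% v 75% cure, the all-randomised difference is only −0.7 points. A large imbalance is needed.
- **That leavers are certainly excluded, and stopping counts for safety only.** The article does not define the per-protocol set, which a fuller document may do, and it does not use the word only. Their exclusion is an inference from the sections set out above.
- **That every high per-protocol success rate under unequal leaving is an error.** With 83% v 75% cure and 25% v 5% leaving, per-protocol succeeds in 82% of trials at 0.05, but the true all-randomised difference is −9 points, inside the margin.
- **That the alpha division inflates error.** It is conservative. It is ill-matched to the hierarchy, and does not by itself show that a per-protocol primary is wrong.

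**Conclusion.** The point holds as a conditional weakness in the decision rule. The article gives intention-to-treat no veto and no rule for disagreement. Two conditions must be met for harm: treatment-related leavers fall outside the per-protocol set (likely, not stated), and leaving is clearly higher on boric acid (assumed). The excess needed is about 13 points if completers are cured equally at 75%, and about 18 to 23 points if boric acid is 8 points better in completers.

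Under those conditions the effect is large: at a true all-randomised difference of −11.25 points, the stated rule succeeds about ten times as often as a rule requiring both sets at one-sided 0.05. These figures count every leaver as not cured. The stated sample size is not wrong on this point. The plan should be changed, because the repair is cheap and recruitment is still open according to Trial status.

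**What to change.** In Statistical considerations, state that:

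1. Day-17 non-inferiority is concluded only if the lower confidence limit for boric acid minus metronidazole is above −10 points in both the per-protocol and the intention-to-treat sets.
2. In intention-to-treat, women who stopped or left for side effects or worsening count as not cured.
3. Losses unrelated to treatment are imputed, not counted as failures. This must stand in the rule itself, because an intention-to-treat analysis of swabbed women only would not expose the problem.
4. As both sets must succeed, alpha is no longer divided between them: the divisor is 2 for the two time points (0.05/2 = 0.025) instead of 4.

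**Cost.** The claim is harder to make at any given alpha: 72% joint power against 79% for per-protocol alone at 0.05 in the scenario of step 6. Removing the needless division more than offsets this there: about 60% joint at 0.025, against about 56% for per-protocol alone at the planned 0.01. No extra women are needed to keep roughly the power the plan now has at its own threshold, but neither figure reaches 80%.

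The reason for each loss has to be recorded. If every loss were simply counted as failure, joint power at 0.025 would fall to about 48% with 25% loss, and 80% joint power would need roughly 155 to 160 per arm (125 to 130 at 0.05).

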## Methods/Design

### Study design

Institutional review board approval was granted for this study through the University of British Columbia Clinical Research Ethics Board (H07-02330). Health Canada Clinical Trial Application Notice of Authorization was obtained on 10 May 2013 (company code 31784, file number 187476). This trial is registered with ClinicalTrials.gov (NCT00799214). This study conforms to CONSORT 2010 guidelines for randomized control trials.

Based on preliminary data, the success rate for the boric acid treatment group is predicted to be approximately 77–88 % [25, 32] in treating BV. Metronidazole would be expected to be 70–80 % [11, 12, 15–18] effective in treating BV, as compared with a 30 % success rate of a placebo group [11, 12]. The Nugent score is found to be >95 % sensitive [33] for detecting BV. We chose a non-inferiority limit of 10 %, as this will allow for a clinically relevant difference between the metronidazole treatment group and the boric acid group. Also, this is approximately 25 % of the expected difference between results obtained for the metronidazole standard treatment group and the placebo group. Accounting for a non-inferiority limit (delta) of 10 %, testing for a significance level of 0.05 and power of 80 %, we require approximately 63 subjects per group. To allow for a dropout rate of 25 %, we set a target rate of 80 subjects per treatment arm. If there is a true difference in favor of the experimental treatment of 8 %, then 126 patients (total for two groups of 63) are needed, to be 80 % sure of the upper limit of a one-sided 95 % confidence interval, using a binary outcome, non-inferiority trial power calculator [34].

We felt it important to include a placebo treatment arm in this study for different reasons: (1) this is the first randomized controlled trial to use intravaginal H_3_BO_3_; thus, comparing it to placebo for safety and effectiveness would be of clinical interest (that is, perhaps it is not comparable to metronidazole in effectiveness but it is still significantly better than placebo), (2) having a placebo group in a non-inferiority trial acts as a sensitivity assay and internal validator for this type of trial [35], (3) comparing metronidazole effectiveness and safety with results obtained for a placebo group in 16–19-year-olds has not previously been done and would also be of clinical interest.

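### The sample size assumes a one-sided 0.05 test, but the analysis section sets a 0.01 threshold that, as counted, includes the primary comparison, and the stated 80% power was not revised

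*Protocol article*

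**What the plan says.** **Sizing (Protocol article, Study design).** The margin is fixed: "We chose a non-inferiority limit of 10" percentage points. The calculation reads "testing for a significance level of 0.05 and power of 80 %, we require approximately 63 subjects per group". It assumes that boric acid is truly better by 8 points, which gives 126 women over the two active arms. The sidedness is explicit, since the stated aim is "to be 80 % sure of the upper limit of a one-sided 95 % confidence interval". For metronidazole minus boric acid the upper limit decides; this is the same as the lower limit for boric acid minus metronidazole against −10 points. The expected control result is a range: "Metronidazole would be expected to be 70–80" per cent. Enrolment is set at 80 per arm to absorb 25% dropout.

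**Analysis (Protocol article, Statistical considerations).** The primary comparison is per-protocol at day 17, judged with a z-based interval for the difference in proportions. It alone determines the non-inferiority result. The secondary efficacy comparisons are intention-to-treat at day 17, and per-protocol and intention-to-treat at day 40. The paragraph on secondary outcomes ends with a Bonferroni-type correction for the two analysis sets and two timepoints: "the threshold for statistical significance will be set at 0.01 (approximately 0.05 divided by 4". Sidedness is not given.

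**Intervals (same section, after the tertiary outcomes).** A short sentence says that 95% "confidence intervals will be established", without naming an analysis or a sidedness.

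**The concern.** In a non-inferiority trial the confidence level is the decision rule: boric acid passes if the limit of the interval clears −10 points, and the level sets how wide the interval is. The article gives one level where it sizes the trial and a stricter one where it describes the tests, and nothing connects the two.

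Two things are at stake. If 0.01 governs the primary test, the trial does not have the power it claims. If it is unclear which level governs, the choice could be made after the results are known, and some plausible results pass at one level and fail at the other.

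**Working it through.** **Inputs**
- From Study design: margin 10 points; true advantage 8 points; one-sided alpha 0.05; power 80%; 63 per group; 80 enrolled per arm; 25% dropout; metronidazole cure 70–80%; boric acid cure 77–88%.
- From Statistical considerations: threshold 0.01, sidedness not stated.
- Assumed: metronidazole cure 75% (midpoint of the range), so boric acid 83%. The article gives no single pair.

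**Step 1: reproduce the plan's figure.**
n = (z₁₋α + z₁₋β)² × [p_c(1−p_c) + p_t(1−p_t)] / (p_t − p_c + 0.10)²
= (1.645 + 0.842)² × (0.1875 + 0.1411) / 0.18² = 62.7, so 63 per group. This matches. With one-sided 0.025 the same formula gives 80, so the trial was sized at one-sided 0.05.

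**Step 2: does the 0.01 threshold include the primary test?** Two analysis sets × two timepoints = 4: per-protocol day 17, intention-to-treat day 17, per-protocol day 40, intention-to-treat day 40. The first is the primary test. The secondary efficacy comparisons alone number three, so a divisor of four on the stated grounds needs the primary test.

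**Step 3: power at the same size.**
Power = Φ(0.18/SE − z₁₋α), with SE = √[(0.1875 + 0.1411)/n].
At n = 63, SE = 0.0722 and 0.18/SE = 2.492. One-sided 0.01: Φ(2.492 − 2.326) = 56.6%. Two-sided 0.01: Φ(2.492 − 2.576) = 46.7%.

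| Evaluable per arm | Cure, metronidazole v boric acid | One-sided 0.05 | One-sided 0.01 | Two-sided 0.01 |
|---|---|---|---|---|
| 63 | 75% v 83% | 80.2% | 56.6% | 46.7% |
| 63 | 70% v 78% | 74.8% | 49.5% | 39.6% |
| 63 | 80% v 88% | 87.0% | 67.2% | 57.8% |
| 60 (80 less 25%) | 75% v 83% | 78.4% | 54.2% | 44.3% |
| 80 (no loss) | 75% v 83% | 87.8% | 68.5% | 59.2% |
| 80 (no loss) | 80% v 88% | 93.0% | 78.7% | 70.8% |

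**Step 4: size needed for 80% power at 0.01 (75% v 83%).** One-sided: 102 evaluable per arm, or 102/0.75 = 136 enrolled. Two-sided: 119 evaluable, or 119/0.75 = 159 enrolled.

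**Step 5: can the level change the conclusion?** Suppose 60 per arm, with observed cure 80% on boric acid and 75% on metronidazole. SE = √[(0.16 + 0.1875)/60] = 0.0761.
- One-sided 0.05: 5 − 1.645 × 7.61 = −7.5 points; non-inferior.
- One-sided 0.01: 5 − 2.326 × 7.61 = −12.7 points; not shown.

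At n = 63 with the planning SE, the smallest observed advantage that passes is 1.645 × 7.22 − 10 = +1.9 points at one-sided 0.05, and 2.326 × 7.22 − 10 = +6.8 points at one-sided 0.01.

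**The case against.** The strongest objection is one of placement. The 0.01 sentence closes the paragraph on secondary outcomes, and the primary paragraph names no threshold. If 0.01 was meant for secondary claims only, the primary test keeps its stated power. This reading cannot be excluded. But the stated grounds for the divisor include the primary test, and nothing exempts it. If an exemption was intended, the divisor is wrong and the text still needs correcting.

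The power figures also rest on an assumed pair of rates. That stands, and is why the range is shown. The lower set further requires 0.01 to be two-sided, which the article does not say; its sizing is explicitly one-sided.

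A reader might infer more than the text supports:
- *Three levels compete for the primary decision.* The 95% sentence follows the tertiary outcomes and names no decision. It may be a reporting convention, or the same one-sided 95% limit used for sizing. The demonstrable conflict is 0.05 against 0.01.
- *The correction is unnecessary because the secondaries are ordered.* The article lists them without a testing order. Without one, adjusting for several claims is a legitimate, conservative choice.
- *Rounding 0.0125 to 0.01 is an error.* The article says the value is approximate and rounds to the stricter side; at 63 per arm (75% v 83%) this moves power only from 59.9% to 56.6%.

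**Conclusion.** The point holds as an unreconciled alpha. The sizing uses a one-sided 95% limit, the analysis section sets 0.01 over a family that by its own count contains the primary test, and the sample size does not follow.

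Under the reading that the count supports, primary power at 63 evaluable per arm is about 57% (49–67% over the stated control range with the 8-point advantage kept), and about 54% at 60 evaluable. Reading 0.01 as two-sided gives about 47% (40–58%) at 63. These figures assume 75% v 83% unless a range is given. The direction does not depend on that pair: even with all 80 per arm evaluable and 80% v 88%, power at one-sided 0.01 is about 79%.

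It would go too far to say that the trial's power simply is 47–57%. That takes one reading of the threshold as settled and fixes rates that the article leaves as ranges.

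**What to change.** Before unblinding, state one alpha, one sidedness and one confidence limit for the primary per-protocol day 17 test, identically in Study design and Statistical considerations. Say whether the 95% intervals mentioned after the tertiary outcomes are for reporting only. Then take one of these routes:

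- **0.01 covers the primary test.** Restate its power as about 54–57% (one-sided, 60 to 63 evaluable per arm), with the assumed rates and the range. Restoring 80% would instead need 102 evaluable per arm, or 136 enrolled in place of 80.
- **0.01 is for the secondary tests only.** Say so, keep the one-sided 95% limit for the primary test, and correct the divisor to the three secondary efficacy comparisons (0.05/3 is about 0.017).
- **Optional: a prespecified fixed sequence at the sizing level,** starting with the primary test. The downside is that later claims are blocked once an earlier one fails. The order needs thought, because the article gives the intention-to-treat day 17 analysis a confirmatory role, yet placed second it could block both day 40 claims.

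Except for any increase in sample size, the cost is a dated wording amendment and no extra participants. Recruitment is already open, so a route that applies a more lenient level to the primary test than the published 0.01 should record its reason and that the decision was made blind to outcome by arm.

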## Abstract

**Background:**

Bacterial vaginosis is associated with increased transmission of sexually transmitted infections, preterm labor, post-surgical infections, and endometritis. Current treatment for symptomatic bacterial vaginosis includes antibiotics, such as metronidazole, which are 70–80 % effective at one month after treatment and result in high recurrence rates and secondary candida infections. Intravaginal boric acid has been used for over a hundred years to treat vaginal infections, such as bacterial vaginosis. Boric acid is inexpensive, accessible, and has shown to be an effective treatment for other infections, such as vaginal candidiasis. To date, there has been no clinical trial evaluation of boric acid effectiveness to treat bacterial vaginosis.

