### Study procedure and data collection

On day 0, a pregnancy test will be conducted and history will be collected by the clinician. During a pelvic examination, the clinician will ensure intact mucous membranes and anatomy, observe whether there is homogenous milky or creamy discharge (one of the four Amsel criteria), take swabs for chlamydia and gonorrhea, BV (for the Nugent score), candidiasis, and trichomonas, and perform a Whiff test using a provided standardized 10 % potassium hydroxide solution (one of the four Amsel criteria). Vaginal discharge will also be tested for pH (one of the four Amsel criteria). Where facilities permit; clue cells will be examined, as the fourth Amsel criterion. On this day, the recruiting clinician will confirm participation, eligibility, and exclusion criteria using provided protocol forms and will collect the signed consent form and the demographic and medical history questionnaires provided.

The blinded treatment pack (containing either H_3_BO_3_ compounded in emollient cream, metronidazole cream, or emollient cream) is allocated by the recruiting clinician in the randomization order to sequential participants on day 0. The participant package also contains: (1) vaginal applicator; (2) pads; (3) non-lubricated non-latex condoms; (4) a diary to record daily use of the treatment (5) information sheet outlining follow-up instructions and emergency contact numbers for the study members. Participants will self-administer the blinded treatment cream intravaginally each evening immediately prior to sleep for 10 days. The participants will be instructed to use a provided pad during day and night. Each participant will record daily compliance, side effects, and symptoms in the journal provided.

On both follow-up visits: days 17–19 (one week after the treatment end) and 40–42 (one month after the treatment end), the participant will return to the clinic that enrolled her for reassessment, a pregnancy test, and a follow-up examination, including a pelvic examination and repeat swab analysis. It will be noted whether her BV symptoms are still present, and if she had any side effects or problems during treatment. The participant will also return her daily treatment diary on the day 17 visit.

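### The article defines major and minor adverse effects inconsistently, so an intolerable effect that does not lead to stopping treatment is a safety failure in one section and minor in another

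*Protocol article*

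**What the plan says.** Five statements in the Protocol article bear on this point.

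- **Outcomes and assessment.** A woman is a failure on the secondary safety outcome by either of two routes: she stops within the 10 days because of side effects, or she complains of side effects that she cannot tolerate. The second route is labelled major. It requires no stopping and carries no clear time limit.
- **Statistical considerations, secondary outcomes.** Safety is described as "safety consideration including intolerable adverse effects requiring patient discontinuation of the 10-day treatment". The Abstract is similar.
- **Statistical considerations, tertiary outcomes.** "Minor adverse effects (side effects not causing the patient to discontinue treatment) will be reported and compared between the treatment arms". The same sentence adds that these effects do not count as treatment failure.
- **Study procedure and data collection.** Dosing is fixed: "Participants will self-administer the blinded treatment cream intravaginally each evening immediately prior to sleep for 10 days". Both follow-up visits, at days 17–19 and 40–42, include "a pregnancy test, and a follow-up examination, including a pelvic examination and repeat swab analysis". The side-effect item at those visits asks "if she had any side effects or problems during treatment".
- **Safety assessments.** For serious adverse effects "during any of the treatments, the study will be put on hold until an investigation can be held". The next sentence says the study stops if serious effects are found to be caused by the treatment, and it states no period.

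**The concern.** The tertiary paragraph separates major from minor by one test: did the effect make the woman stop? Outcomes and assessment uses a different test as one of its two routes: was the effect intolerable? The two tests part company whenever a woman has an intolerable effect and does not stop. After the tenth dose there is nothing left to stop, so every intolerable effect that begins later falls into this gap.

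The number of safety failures per arm is at stake. Two analysts who each follow the article faithfully could report different counts. If the choice is left until the data are in, it may be made with the results in view. Women with the same complaint may also be classed by when it arose and not by how bad it was. The narrow wording of the visit question adds to this, because an event that begins after dosing may not be asked about at all.

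**Working it through.** The article gives no figure for the safety outcome. Its only sample-size calculation concerns cure and has no bearing here. The check is therefore to put typical cases through each definition.

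| Case | Outcomes and assessment | Secondary outcome text | Tertiary outcome text |
|---|---|---|---|
| A. Intolerable effect, stops before day 10 | Safety failure (first route) | Counted | Not minor |
| B. Intolerable effect during dosing, completes the course | Major, safety failure (second route) | Not named | Minor, not a failure |
| C. Intolerable effect starting after the tenth dose, such as symptomatic yeast infection found at day 17–19 | Major, safety failure if she complains of it as a treatment effect | Not named; no doses remain | Minor, not a failure |
| D. Tolerable effect, completes the course | Not a failure | Not named | Minor, not a failure |

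The sections agree on A and D and conflict on B and C.

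**Effect on the count.** In one arm, let D be the women who stop because of an intolerable effect, and I the women who have an intolerable effect but do not stop.

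- Failures under Outcomes and assessment: D + I
- Failures if only effects causing discontinuation count: D
- Difference: I

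The documents do not give I. With the planned 80 women per arm, each such woman moves the failure proportion by 1/80 = 1.25 percentage points. If the anticipated 25% are lost, 80 × 0.75 = 60 remain and the step is 1/60 = 1.7 points. As an assumed range only, I = 1 to 8 of 80 gives 1.25 to 10 points.

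**Time in which case C can arise.** Dosing takes 10 days.

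- To the primary visit at day 17: (17 − 10)/17 = 41% of the time lies after dosing.
- To the last visit: (40 − 10)/40 = 75%, or (42 − 10)/42 = 76%.

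These are shares of calendar time, not of events.

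**Data capture.** The day 5 contact falls within dosing. The diary records daily use and side effects and is handed in at the day 17 visit. After that, information on later effects comes from the visits, where the side-effect item is worded for the treatment period. The examination and swabs may still find new conditions, but nothing says how they would be classed.

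**The case against.** The strongest defence is that this is a condensed article. Coding and tabulation of adverse events commonly sit in the full protocol or SAP, and their absence here is no finding. That is right, but the point does not rest on absence: the article states two tests that conflict.

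A second defence is that the secondary text is introduced by the word including, so it need not exclude the second route in Outcomes and assessment. This also stands, and it softens the conflict between those two places. It does not help the tertiary paragraph, which classes by discontinuation alone.

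A reader might infer more than the documents support:

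- *Harm after dosing can only be minor.* The second route in Outcomes and assessment shows otherwise.
- *Harm after dosing is never compared.* Minor effects are to be compared between arms, and the tertiary outcomes also test safety of boric acid against placebo with no time window.
- *Fewer yeast infections is the trial's rationale.* The Abstract says that current antibiotics "result in high recurrence rates and secondary candida infections". That is one background drawback. The stated objective is cure of bacterial vaginosis, and the Discussion names lower cost as the benefit.
- *A serious reaction after day 10 can never halt the study.* The hold wording could mean the dosing days or any of the three arms, and the stop sentence after it has no window. The text is unclear and does not plainly exclude the later period.
- *Candidiasis must become a new secondary outcome.* That is a preference. The follow-up swabs are not itemised. By day 40–42 the comparison would be confounded, because symptomatic failures at day 17–19 receive other medication, and only 30% success is expected on placebo.

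**Conclusion.** The concern holds as an inconsistency of definition. An intolerable effect that does not lead to stopping is major and a safety failure under Outcomes and assessment, and minor and not a failure under the tertiary outcomes. The reported safety failure count therefore depends on the section followed, by 1.25 percentage points per affected woman in an arm of 80. How many women this concerns cannot be derived from the documents. The 41% and 75–76% figures show only how long the ambiguous period lasts.

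The conclusion assumes that a complaint of intolerable effects after the tenth dose can qualify under the second route, which the text allows but does not spell out. For effects during dosing in women who complete the course, the conflict needs no such assumption. The primary cure comparison is not touched, since it rests on the Nugent score. The matter should be corrected because it governs a secondary outcome and is cheap to resolve.

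**What to change.** 1. Use one definition in the Abstract, Outcomes and assessment, and both parts of Statistical considerations. Class effects as major or minor by severity (intolerable or not), whether or not doses remained to stop.
2. State that the safety outcome covers day 0 to day 40–42.
3. Word the side-effect question at both follow-up visits to cover the time since the last contact.
4. Report new candidiasis found at the planned visits within the same between-arm safety comparison. Read the day 40–42 results with caution because of the medication given to failures at day 17–19.
5. Reconcile the hold rule and the stop rule in Safety assessments on the period each covers. Which rule is right is for the sponsor to decide.

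The cost is mainly wording, a revised visit form and a small addition to the safety table, with no new visits. The definition should be settled before the randomization code is released for analysis. Recruitment is already open, so women seen before the change will have been asked the narrower question, and the report should say so. The count of major events may rise in some arms.
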